##### **13.1.2 Per-Protocol Cohort**

Per-protocol cohort will include all patients who have completed the treatment prescribed in the protocol or those without major violations of the trial protocol. The exact definition of major protocol violation will be finalized during data review, generally including, but not limited to the following conditions: failure to meet the primary inclusion criteria, treatment that seriously interferes with efficacy evaluation after enrollment, poor compliance, and follow-up that seriously exceeds the time window. Per-protocol population will be the secondary population for efficacy evaluation.

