- 299 2. The patient's symptoms worsened after medication, and in order to protect the patient, the patient was
- 300 withdrawn from the study and received other effective treatment;
- 301 3. Patients experience some comorbidities, complications, or special physiological changes during the study,
- 302 affecting the efficacy and safety evaluations;

4. Patients with poor compliance during the study, i.e., underdosing by less than 70% or overdosing by more than 130% of the required doses;
5. Patients who are midway breaking the blindness during the study for any reasons;
6. Patients who are considered not suitable to continue the study as judged by the investigator.

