#### **6.2.3 Elimination Criteria**

Patients who should not have been enrolled or who have completed the study but violated some of the requirements of the protocol during the study will be eliminated as judged by investigators, including patients who:

1. Have not taken the drug;
2. Have no test records after drug administration;
3. With unavailable efficacy and safety evaluations due to the administration of a certain prohibited drug.

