#### **13.1 Analysis Cohorts**

##### **13.1.1 Modified Intention-To-Treat Cohort**

According to the basic principle of intention-to-treat analysis, all patients after randomization who received at least one record for drug administration and efficacy evaluation will be included in the modified intention-to-treat cohort. During analysis with the modified intention-to-treat cohort, missing values will be estimated using the last observation carried forward method. The modified intention-to-treat population will be the primary population for efficacy evaluation in this study.

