### 13.3 Sample Size Determination

Based on previous findings, assuming that the proportion of patients in the control group with mRS  $\leq 2$  at 3 months is 45%, and the proportion in the XST group is relatively increased by 12%, with the significant level of 0.05 and the power of 0.80, 1342 patients are required in each group, and considering 10% lost to follow-up, 1492 patients are required in each group. Rounded to an integer, this trial is expected to enroll 3000 patients.

| Power  | Sample size
of the XST
group | Sample size
of the control
group | Response
rate of IMP | Response rate
of control
drug | Difference in
response rate
between the two
groups | Significant
level |
|--------|------------------------------------|----------------------------------------|-------------------------|-------------------------------------|-------------------------------------------------------------|----------------------|
| 0.8000 | 2389                               | 2389                                   | 0.4400                  | 0.4000                              | 1.100                                                       | 0.0500               |
| 0.8000 | 1931                               | 1931                                   | 0.4950                  | 0.4500                              | 1.100                                                       | 0.0500               |
| 0.8001 | 1565                               | 1565                                   | 0.5500                  | 0.5000                              | 1.100                                                       | 0.0500               |
| 0.8001 | 1977                               | 1977                                   | 0.4440                  | 0.4000                              | 1.110                                                       | 0.0500               |
| 0.8002 | 1597                               | 1597                                   | 0.4995                  | 0.4500                              | 1.110                                                       | 0.0500               |
| 0.8002 | 1293                               | 1293                                   | 0.5550                  | 0.5000                              | 1.110                                                       | 0.0500               |

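### Section 13.1.2 joins the two per-protocol conditions with *or*, so read literally a listed major violation excludes no one who completed treatment, in conflict with section 6.2.3

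*Protocol*

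**What the plan says.** Protocol section 13.1.2 defines the per-protocol cohort: it will "include all patients who have completed the treatment prescribed in the protocol or those without major violations of the trial protocol". The exact meaning of a major violation is left to the data review, with an open list of examples: "failure to meet the primary inclusion criteria, treatment that seriously interferes with efficacy evaluation after enrollment, poor compliance", and follow-up seriously outside the time window. On the role of the set the section says: "Per-protocol population will be the secondary population for efficacy evaluation". Section 13.1.1 gives the first place to another set: "The modified intention-to-treat population will be the primary population for efficacy evaluation in this study".

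Section 6.2.3, on elimination criteria, covers patients who should not have been enrolled and those "who have completed the study but violated some of the requirements of the protocol during the study will be eliminated as judged by investigators". It does not say from which analysis set they are eliminated.

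No other section restates the per-protocol definition with *and*.

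**The concern.** A per-protocol set is normally the patients who both received the planned treatment and have no deviation serious enough to disturb the comparison. The sentence in 13.1.2 makes each condition sufficient by itself. The violation list that follows then does no work for a patient who completed treatment, however long it becomes at the data review.

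At stake is what a per-protocol result can be taken to show. If it is reported beside the primary analysis as the result in patients treated and assessed as planned, some of those patients may not fit that description. There is also an avoidable choice. With 13.1.2 and 6.2.3 pulling in different directions, someone must decide which rule to apply, and that decision should not be open once results by group are known.

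**Working it through.** **1. The protocol's own figure, which does not depend on this point.** Section 13.3 assumes 45% with mRS ≤ 2 in the control group and a relative increase of 12%, so 0.45 × 1.12 = 0.504. With two-sided alpha 0.05, power 0.80, pooled variance and no continuity correction:

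n = [1.960 × √(2 × 0.477 × 0.523) + 0.8416 × √(0.45 × 0.55 + 0.504 × 0.496)]² / 0.054² ≈ 1342 per group.

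Then 1342 / 0.90 rounds up to 1492. Both match section 13.3. Neither uses the per-protocol set, so nothing below changes them.

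**2. The rule as logic.**

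| Completed treatment | Major violation | *or* (as written) | *and* |
|---|---|---|---|
| yes | no | in | in |
| yes | yes | in | out |
| no | no | in | out |
| no | yes | out | out |

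The two rules differ in the middle rows: completers with a violation, and non-completers without one.

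**3. Which patients fall in those rows under the rest of the protocol.**

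- *Ineligible completers.* Section 8.3 lets a patient enrolled by mistake stay on treatment when this is judged harmless. Such a patient can complete treatment and enters by the first condition, although failed inclusion criteria are on the list.
- *Completers assessed seriously out of window.* Section 6.1.3 sets Month 3 ± 7 days for the visit that carries the primary outcome. Completion alone admits the patient, whatever the visit date.
- *Poor compliers.* Section 6.2.1 makes poor compliance a ground for withdrawal, with limits worded as "underdosing by less than 70% or overdosing by more than 130% of the required doses", and section 7.6.2 makes it a ground for permanent discontinuation. Such patients generally do not complete and have a listed violation. They fail both conditions and are out even under *or*.
- *Users of prohibited panax notoginseng products.* Section 7.4.1 takes them off study treatment. Once this is classed as a major violation, they too fail both.
- *Early stoppers.* Section 7.6.2 allows stopping by patient choice or for a related adverse event, with follow-up continuing. They enter by the second condition only if stopping is not classed as a major violation. If poor compliance is judged on the share of all required doses with a 70% lower limit (an assumption, since 13.1.2 does not cite the limits in 6.2.1), a patient who stops before about 0.7 × 3 = 2.1 months is a poor complier and is out. Later stoppers could remain in.

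**4. Set against section 6.2.3.** For a completer with a serious violation, 13.1.2 says include; 6.2.3 says eliminate if the investigator so judges. Both cannot govern the same set.

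**5. Size.** The protocol gives no completion or violation rates, so the following is illustration only. Let *a* be the share not completing, *b* the share with a major violation and *f* the share failing both. The *or* rule leaves out *f*; the *and* rule leaves out *a* + *b* − *f*. They differ by *a* + *b* − 2*f*, where *f* runs from 0 to the smaller of *a* and *b*. On 3000 patients:

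| Complete / violation-free (assumed) | Full overlap | Independent | No overlap |
|---|---|---|---|
| 95% / 95% | 0 | 0.095 → 285 | 0.10 → 300 |
| 90% / 90% | 0 | 0.18 → 540 | 0.20 → 600 |
| 80% / 90% | 0.10 → 300 | 0.26 → 780 | 0.30 → 900 |
| 80% / 85% | 0.05 → 150 | 0.29 → 870 | 0.35 → 1050 |

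Example, 80% / 85% under independence: *f* = 0.20 × 0.15 = 0.03, and 0.20 + 0.15 − 0.06 = 0.29.

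**The case against.** The strongest reply is that *or* is a slip of drafting or translation, and that 6.2.3 shows the intention to remove violators. That is likely, and it supports the correction. It does not cure the rule: 6.2.3 leaves elimination to the investigator's judgement and names no analysis set, while 13.1.2 is the section an analyst will follow to build the cohort.

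A second reply is that membership is settled case by case at the data review, that section 8.5 provides for a blind review before the database is locked, and that a statistical analysis plan not shown here may word the rule properly. But 13.1.2 defers only the meaning of a major violation, not the connector. An analysis plan that wrote *and* would depart from the protocol.

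A third reply stands in large part. A reader might infer that the violation list becomes empty or that early stoppers in general get in. Sections 6.2.1, 7.4.1 and 7.6.2 do not support that: poor compliers and users of prohibited products are taken off treatment and would generally fail both conditions. The defect is clearest for the ineligible and out-of-window completers.

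**Conclusion.** The per-protocol membership rule is wrong as written and conflicts with section 6.2.3. If followed, it admits completers with listed major violations and some early stoppers, and so weakens the set as the secondary efficacy population. That conclusion needs only the wording and no assumed rates.

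The size is not known. A reader might infer that the cohort would nearly coincide with the primary set, that agreement between the two would be automatic, or that many hundreds of patients would be wrongly kept. Those inferences need assumed rates together with independence, or less overlap still, between non-completion and violation. The protocol makes independence implausible, because poor compliance is both a listed violation and a reason for stopping treatment. Under full overlap at 80% / 85% the *or* set keeps only the larger share, 85%, so it would still drop 15% of patients. Over assumed ranges of 80–90% completing and 85–90% violation-free, full overlap leaves a difference of 0 to 10 points.

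Nor is the set shown to be useless: the protocol calls it only the secondary population. The primary analysis, the safety cohort and the sample size are unaffected. This should be corrected, but it does not threaten the primary conclusion.

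**What to change.** In section 13.1.2, define the per-protocol cohort as patients who completed the prescribed treatment **and** had no major protocol violation. In section 6.2.3, name the analysis set to which elimination applies, so that the two sections give the same answer for a completer with a violation. State that the list of major violations, including whether and when early stopping counts, is finalised at the blinded data review before unblinding. Carry the same wording into the statistical analysis plan.

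The cost is one connector, one cross-reference and one sentence on timing. The per-protocol set becomes somewhat smaller and its intervals slightly wider.

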##### **13.1.3 Safety Cohort**

Safety cohort is defined as a collection of all patients who have received at least one dose of drug treatment.

#### **13.2 Statistical Analysis Methods**

##### **13.2.1 Baseline Between-Group Comparisons**

Wilcoxon rank-sum test will be used for measurement data. Chi-square test will be used for the comparability of enumeration data between the two groups.

##### **13.2.2 Efficacy Analysis**

Primary endpoint: According to the basic principle of intention-to-treat analysis, Chi-square test or Fisher's exact test will be used for data in the modified intention-to-treat cohort to evaluate efficacy. In addition, a logistic regression model will be adopted to calculate the odds ratio (OR) between the two treatment regimens, with center effects set as random effects in the model.

Secondary endpoint: The primary endpoint analysis strategy will be used for most secondary endpoint analyses. Wilcoxon rank-sum test will be used for measurement data to analyze differences between the two groups. For survival data, the Kaplan-Meier method will be used to estimate the survival rate of each group and plot survival curves, log-rank test will be used for efficacy evaluation, and Cox proportional hazards model will be used to calculate the hazard ratio (HR) between the two treatment regimens. For non-survival data, Chi-square test or Fisher's exact test will be used, and a logistic regression model will be used to calculate the OR value. Center effects will be set as random effects in all the models.

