## 145 2. Hypothesis

146 For patients with ischemic stroke within 14 days of onset, XST can further improve the 90-day functional  
147 outcome.

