## 200 **4. Outcomes**

### 201 **4.1 Primary Efficacy Outcome**

202 Proportion of patients with functional independence ( $mRS \leq 2$ ) at 3 months after randomization.

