### 203 **4.2 Secondary Efficacy Outcomes**

- 204 1. Proportion of recurrent stroke (ischemic stroke and intracerebral hemorrhage) at 3 months and 12 months
- 205 after randomization;
- 206 2. Proportion of patients with functional independence ( $mRS \leq 2$ ) at 12 months after randomization;
- 207 3. Proportion of patients with no or minimal disability ( $mRS \leq 1$ ) at 3 months and 12 months after
- 208 randomization;
- 209 4. Change in NIHSS score at 3 months after randomization;
- 210 5. Proportion of composite cerebrovascular events (ischemic stroke, intracerebral hemorrhage, myocardial
- 211 infarction, and vascular death) at 3 months and 12 months after randomization;
- 212 6. Difference of EuroQoL Group 5-Dimension (EQ-5D) score at 3 months and 12 months after
- 213 randomization;
- 214 7. Change in Barthel Index (BI) score at 3 months and 12 months after randomization;
- 215 8. Difference of platelet counts and coagulation indicators (prothrombin time, and activated partial
- 216 thromboplastin time) at 3 months after randomization.

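### Every listed mRS outcome is a two-way cut of a seven-grade scale; an ordinal analysis should be the first secondary outcome, with the primary left as it is

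*Protocol*

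**What the plan says.** Section 2 states a general hypothesis, that "XST can further improve the 90-day functional" outcome; it names no threshold. Section 6.1 schedules the mRS on Day 1 and at 1, 3, 6 and 12 months. Appendix 2 defines all seven grades, with death as 6.

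The listed mRS outcomes are:

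- Section 4.1, primary: "Proportion of patients with functional independence", that is mRS 2 or lower, at 3 months.
- Section 4.2, item 2: the same cut at 12 months.
- Section 4.2, item 3: "Proportion of patients with no or minimal disability", that is mRS 1 or lower, at 3 and 12 months.

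For the primary, section 13.2.2 states that "Chi-square test or Fisher's exact test will be used for data in the modified intention-to-treat cohort to evaluate efficacy", and adds a logistic odds ratio with centre as a random effect. Most secondary outcomes follow the same strategy. The rank-sum test is reserved for measurement data, and the mRS outcomes are defined as proportions.

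Section 13.3 takes 45% v 50.4% at mRS 2 or lower and concludes that "with the significant level of 0.05 and the power of 0.80, 1342 patients are required in each group". With 10% loss this becomes 1492, rounded to 3000 in total.

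**The concern.** The trial asks whether function improves, records function on an ordered seven-grade scale, and then uses only two of the six possible division points, one at a time. A patient who moves from grade 5 to grade 3, or who survives in grade 5 instead of dying, changes no mRS result at either cut. The sample size assumes that 55% of control patients are in grades 3 to 6.

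The second cut is also a weak companion to the first. It repeats the same kind of comparison at a threshold that may hold few patients, whereas the whole scale, already collected, could be compared at the cost of one model.

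**Working it through.** **The plan's own figure.** Inputs from section 13.3: p0 = 0.45, p1 = 0.45 × 1.12 = 0.504, alpha 0.05 (two-sided, section 13), power 0.80. With mean rate 0.477 and the pooled formula:

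n = [1.960 × √(2 × 0.477 × 0.523) + 0.8416 × √(0.45 × 0.55 + 0.504 × 0.496)]² / 0.054² = (1.3844 + 0.5936)² / 0.002916 = 1341.8, so 1342. Then 1342 / 0.9 = 1491.1, so 1492.

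Both figures reproduce. Chi-square power is 0.800 at 1342 per group and 0.842 at 1500.

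**Effect as an odds ratio.** (0.504/0.496) / (0.45/0.55) = 1.242; log = 0.2167.

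**Two assumptions, neither in the protocol.** (a) The odds ratio of 1.242 applies at every mRS threshold. (b) The control distribution over grades 0 to 6 is one of the five below, each with 45% at 2 or lower.

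**Formulas.** Ordinal power (Whitehead) = Φ{log OR × √[n(1 − Σp̄³)/6] − 1.960}, where p̄ is the mean of the two groups' probabilities in each grade. Example, distribution C: Σp̄³ = 0.0356, so 0.2167 × √(1342 × 0.9644/6) − 1.960 = 3.182 − 1.960 = 1.222, and the power is 0.889. For the cut at 1, the same odds ratio moves 25% to 29.3% (odds 0.3333 × 1.242 = 0.414), and the two-proportion test at 1342 has power 0.70.

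| Control distribution, grades 0-6 (%) | Ordinal, 1342 | Ordinal, 1500 | Cut at 2, 1342 | Cut at 1, 1342 (control rate) |
|---|---|---|---|---|
| A: 15, 15, 15, 13.75 × 4 | 0.89 | 0.92 | 0.80 | 0.75 (30%) |
| B: 5, 20, 20, 25, 20, 7, 3 | 0.89 | 0.92 | 0.80 | 0.70 (25%) |
| C: 10, 15, 20, 25, 20, 6, 4 | 0.89 | 0.92 | 0.80 | 0.70 (25%) |
| D: 3, 12, 30, 35, 15, 3, 2 | 0.88 | 0.91 | 0.80 | 0.55 (15%) |
| E: 2, 5, 38, 45, 8, 1, 1 | 0.85 | 0.89 | 0.80 | 0.32 (7%) |

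Simulated tie-corrected rank-sum tests agree with the formula to within about 0.005. The ordinal comparison reaches 80% power with about 1025 (A) to 1173 (E) per group.

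**If the odds ratio is not common.** Distribution C, 1342 per group, odds ratio 1.242 kept at 2/3, log odds ratios at all other thresholds reduced (ordinal power by simulation):

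| Other log odds ratios, relative to 2/3 | Ordinal | Cut at 2 | Cut at 1 |
|---|---|---|---|
| 90% | 0.84 | 0.80 | 0.61 |
| 80% | 0.78-0.79 | 0.80 | 0.51 |
| 70% | 0.72-0.73 | 0.80 | 0.41 |
| 50% | 0.57-0.59 | 0.80 | 0.23 |
| 0% (only grade 3 to 2) | 0.20 | 0.80 | none beyond alpha |

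In the last case, seven assumed control distributions gave ordinal power from 0.11 to 0.55. The ordinal test beats the cut at 1 in every row. It beats the cut at 2 only while the effect is close to common.

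**The case against.** The strongest reply is that this is an efficiency choice and not an error. Endpoint, test and sample size agree with each other, and the trial meets its own 80% target. The cut at 2 has a clinical meaning that Appendix 2 supports: grade 2 patients look after themselves, while grade 3 patients need some help. The statistical analysis plan is not shown and may contain a shift analysis. All of this stands. It is why the primary should not change. The point survives because section 4.2 is the protocol's declared list of secondary outcomes and section 13.2.2 fixes how they are tested; an ordinal result added elsewhere would lack that standing.

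A reader might also infer three stronger things that the documents do not support.

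- That the trial gives up 5 to 9 points of power under its own effect. The plan fixes only 45% v 50.4% at one threshold; a common odds ratio and a grade distribution have to be added.
- That the trial is blind to change within grades 3 to 6. This is true of the mRS outcomes only. Section 4.2 lists Barthel Index, NIHSS, EQ-5D and a composite that includes vascular death, and section 4.4 lists all-cause mortality. The narrower point is that the Barthel, NIHSS and EQ-5D forms in the appendices have no category for death. Of these scales, only the mRS ranks disability and death together, and no listed analysis uses that ranking.
- That patients already at mRS 2 or lower on Day 1 can benefit only by crossing to 1 or lower. The primary is status at 3 months, so preventing a decline to 3 or worse also counts.

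**Conclusion.** The point holds as an improvement to the secondary outcomes. The listed mRS analyses are one primary cut, the same cut repeated at 12 months, and one new cut at both times; none registers movement within grades 3 to 6. Under an assumed common odds ratio of 1.242 and assumed control distributions, an ordinal comparison has about 85-89% power at 1342 per group (89-92% at 1500). The cut at 2 has 80% (84% at 1500), and the cut at 1 has about 32-75% at 1342.

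The case against the cut at 1 is firm over the scenarios examined. An effect stronger at 1/2 than at 2/3 was not examined, which is one reason to keep that cut as supportive. The case against the cut at 2 is conditional: the ordinal advantage is gone when the other log odds ratios are about 80% of that at 2/3, and turns into a large loss if benefit is only movement from grade 3 to 2. A reader might conclude that the ordinal test should become primary. The documents give no basis for choosing between these patterns, so that does not follow.

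**What to change.** In section 4.2 (item 3) and section 13.2.2:

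1. List the full mRS distribution (0 to 6, death = 6) at 3 and 12 months as the first secondary outcome.
2. Compare the groups with a proportional-odds logistic model with centre as a random effect, and report the common odds ratio with its 95% confidence interval.
3. Report the rank-sum (win-odds) estimate alongside in all cases, so that the choice of summary does not depend on a test of proportionality made on the data.
4. Keep mRS 1 or lower at 3 and 12 months as a supportive outcome.

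The primary outcome, its test and the 3000 patients stay as they are. No new data or visits are needed. The cost is the wording in two sections, one more model, a lower rank for mRS 1 or lower, and a common odds ratio that rests on approximate proportionality. The change does not raise the power of the primary test; it gives the section 2 hypothesis a declared analysis that uses the whole scale.

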### 465 **8.2 Randomization Procedures**

466 For patients eligible for randomization, each center will assign randomization codes in strict sequential order.  
467 Randomization codes will be generated by SAS 9.4 (SAS Institute, Inc, Cary, NC) through block randomization  
468 to achieve balance in the allocation of patients between the two groups (1:1) as much as possible. The number of  
469 randomized patients planned in this study is approximately 3000.

470 At the Visit 1, the investigator will provide the randomization codes of patients to the dedicated drug-  
471 distributing employees in the sequence of patient enrollment, and the employees will identify the unique  
472 identification number on the drug box for drug supply at Visit 1. Patients will be required to complete the first  
473 administration of the IMPs within 24 hours after randomization.

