### **13. Statistical Analysis and Sample Size**

All statistical analyses will be carried out using the SAS 9.4 (SAS Institute, Inc, Cary, NC) software according to the predetermined statistical analysis plan. Comparisons between two groups are performed using a two-side test ( $\alpha = 0.05$ ). A difference of  $p \leq 0.05$  is considered to be statistically significant.

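### The primary test is an unadjusted chi-square that forgoes available power by using no baseline covariate, and its p-value comes from a different analysis than the odds ratio

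*Protocol*

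**What the plan says.** The primary outcome (Protocol 4.1) is binary: "Proportion of patients with functional independence", meaning mRS 2 or less, at 3 months. Section 13.2.2 tests it with a chi-square or Fisher's "exact test will be used for data in the modified intention-to-treat cohort to evaluate efficacy". It then describes a second analysis: "In addition, a logistic regression model will be adopted to calculate the odds ratio (OR) between the two treatment regimens". Centre enters this second analysis as a random effect and does not enter the test. No baseline covariate is named for either analysis. Section 13 sets the level at 0.05: "Comparisons between two groups are performed using a two-side test".

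On allocation, section 8.2 says that "each center will assign randomization codes in strict sequential order", with block randomisation at 1:1.

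Eligibility (3.3) covers NIHSS 4 to 15, age 18 to 75 and up to 14 days from onset. The visit schedule (6.1) and the Visit 1 list (6.1.1) include demographics and NIHSS on Day 1, and 6.1.1 makes the Visit 1 results the baseline values. Time from onset is not listed as an item of its own.

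For continuous secondary outcomes, 13.2.2 says that a "Wilcoxon rank-sum test will be used for measurement data to analyze differences between the two groups". Section 4.2 defines the NIHSS and Barthel outcomes as changes and the EQ-5D outcome as a difference in score at 3 and 12 months.

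**The concern.** The eligible population is wide in severity, age and time since onset, so the chance of independence at 3 months may differ considerably between patients for reasons recorded before treatment. The decisive test uses none of that information. If those baseline values are prognostic, the trial gives up power that would need no extra patient or visit, and a chance imbalance between the arms stays uncorrected in the primary result.

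There is also a question of coherence. The p-value comes from a test with no centre term, while the odds ratio and its confidence interval are conditional on centre. In a borderline trial one could be significant and the other not, and the protocol does not say how such a result would be reported.

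**Working it through.** **1. The protocol's own figure.** Section 13.3 assumes that the control proportion at 3 "months is 45%, and the proportion in the XST group is relatively increased by 12" per cent, so p0 = 0.45 and p1 = 0.45 × 1.12 = 0.504. The difference is 0.054 and the mean 0.477. For the pooled two-proportion test without continuity correction:

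n = [1.960 × √(2 × 0.477 × 0.523) + 0.8416 × √(0.45 × 0.55 + 0.504 × 0.496)]² / 0.054²
= (1.3844 + 0.5936)² / 0.002916 = 1341.8, so 1342 per group.

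For 10% loss, 1342 / 0.90 = 1491.1, so 1492. Both match the protocol. Power is 0.8001 at 1342 per group, and 0.842 if all 1500 per group were evaluable. The trial is therefore sized for exactly the unadjusted test that it names.

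**2. Power forgone.** The protocol gives no prognostic strength for NIHSS or age, so it is assumed and shown as a range. Trials of 1342 per group were simulated (12,000 per setting) with one standard-normal baseline score acting on the logit. Intercept and treatment effect were solved so that the marginal rates stayed at 45% and 50.4%. The chi-square was compared with the Wald test from a logistic model adjusted for the score.

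| Slope per SD (assumed) | AUC of score | Chi-square power | Adjusted power | Gain (points) | Conditional OR |
|---|---|---|---|---|---|
| 0 | 0.50 | 0.798* | 0.798* | 0 | 1.24 |
| 0.5 | 0.63 | 0.805 | 0.824 | 1.9 | 1.26 |
| 0.9 | 0.72 | 0.806 | 0.861 | 5.5 | 1.29 |
| 1.25 | 0.78 | 0.802 | 0.896 | 9.5 | 1.33 |
| 1.6 | 0.83 | 0.804 | 0.925 | 12.0 | 1.37 |

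*4000 trials. The Monte Carlo standard error at 12,000 trials is √(0.8 × 0.2 / 12,000) = 0.004.

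In patient terms, an unadjusted test reaches power 0.82 with 1342 / 0.95 = 1413 per group, and 0.90 with 1342 / 0.75 = 1789 per group.

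A second simulation drew NIHSS on 4 to 15, with 1350 per arm and 3000 trials per setting. It gave 0.82, 0.85, 0.87 and 0.90 at AUC 0.64, 0.70, 0.73 and 0.78. Its null check gave rejection rates of 0.051 and 0.053 for the two tests, so adjustment did not inflate the type I error.

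The marginal odds ratio is (0.504 / 0.496) / (0.45 / 0.55) = 1.242. The adjusted odds ratio rises from this as the covariate becomes more prognostic, although the risk difference stays at 5.4 points. The two odds ratios therefore estimate different quantities.

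**3. How often test and centre model disagree.** A centre-stratified Mantel-Haenszel test stood in for the random-centre model, with about 1340 per arm, balanced within centre, in 30 or 67 centres. The number of centres and the between-centre SD on the logit scale are assumptions. At 45% versus 50.4%, the verdicts at 0.05 differed in:
- about 0% of trials at SD 0;
- up to 1.0% at SD 0.3;
- 1.0 to 1.5% at SD 0.5;
- about 3 to 4% at SD 0.8.

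Under the null they differed in at most about 1.3%.

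**The case against.** The strongest reply is that nothing here is an error. Under 1:1 randomisation the chi-square holds its level. With allocation balanced within centre and centres that differ, it is if anything conservative: null rejection in the centre simulations was 0.036 to 0.051. The trial was sized for this test and delivers 80% on its own assumptions. All of that stands, so a reader who inferred that the primary test is invalid or the trial underpowered would be going beyond the documents.

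Other stronger readings also fail:

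- **That centre is ignored.** This is true of the test only. Section 13.2.2 puts a random centre effect in every model.
- **That there are two rival primary results.** The protocol gives them separate roles, the test to judge efficacy and the model to supply the odds ratio. What remains is that they can occasionally disagree.
- **That every useful covariate is already collected.** This is documented for NIHSS and age, and centre is known for each patient. Time from onset is only implied by the 14-day criterion.
- **That the secondary scales are analysed without baseline.** NIHSS and Barthel are change scores, so baseline enters by subtraction. Only for EQ-5D is no baseline term stated.

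It can also be said that covariate lists belong in the statistical analysis plan, which is not at hand. That is fair for details of the logistic model. It does not reach the choice of primary test, which the protocol itself fixes as unadjusted.

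Finally, the gain rests on an assumed prognostic strength. NIHSS here is restricted to 4 to 15 and may be measured up to 14 days after onset, and the simulations used a single, correctly specified covariate without centre. The low end of the range cannot be ruled out.

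**Conclusion.** The point holds as one of efficiency and coherence, not of validity. The primary test is sound and correctly sized, but a better one is available from data that the trial already collects. At 1342 per group, adjustment would move power from about 0.80 to between about 0.82 and 0.92, a gain of about 2 to 12 points, for an assumed AUC of about 0.63 to 0.83. The gain is zero if the covariates carry no prognostic information. Disagreement between the p-value and the odds ratio is a minor matter, at about 0 to 4% of trials under the assumed centre variation, but it is avoidable. The change is worth making. The confidence lies in the reading of the text and the direction of the gain, not in its exact size.

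**What to change.** Before unblinding, name one primary analysis: a logistic model with treatment, baseline NIHSS as a continuous term, age and a random intercept for centre. Add time from onset to randomisation if it is recorded. Take both the p-value and the effect estimate from this model. Because its odds ratio is conditional on the covariates, report a standardised risk difference with a 95% confidence interval beside it. Keep the chi-square or Fisher test as a supportive analysis.

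For NIHSS and Barthel, replace the rank-sum test on change with ANCOVA or rank ANCOVA on the Day 1 value, which is more efficient. Use the same approach for EQ-5D, which brings its Day 1 value into the comparison.

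The cost is wording in the protocol or statistical analysis plan. No patients or visits are added. The sample size can stay as it is, since it already gives 80% power without adjustment. The one item to confirm is whether onset time is recorded.
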